**Figure 1 F1:**
[figure not shown]
Flow chart of the DREAM trial.

### Study on antibiotic resistance of oral streptococci

In a subgroup of adult patients suffering from odontogenic infections, microbiological analyses on antibiotic resistance of oral streptococci are conducted. Intraoral swabs from the buccal mucosa will be collected of these study patients at three points in time: at the first consultation due to an odontogenic infection (T0), after two weeks (T1), and after six months (T2). The swabs will be transported at room temperature to the accredited diagnostic laboratory within two hours. There, the swabs will be streaked onto sheep blood agar plates. After 48 hours of incubation under a CO2-enriched atmosphere, samples from every morphologic type of alpha-hemolytic colonies will be gained for species identification and for determination of the antibiotic resistance profile. For each patient, the temporal changes in present oral streptococcal species and antibiotic resistance profiles will be recorded.

In the context of the overall cRCT, objective information about antibiotic resistance development will be correlated to antibiotic prescribing behaviour of dental care practices. This information will be communicated to dentists (via feedback) to enhance positive competition. For this subgroup, we intend to include a total number of 500 patients suffering from odontogenic infections. Among these patients, several secondary outcomes will be assessed. These include severity of the infection (judged by the dentist), pain severity, duration of therapy, re-consultation rate, adverse drug events (with reference to antibiotics), complications, and antibiotic resistance developments.

### Data collection, completeness, and quality

Data collection will be based on practice software. In Germany, dentists make use of a large variety of software packages. Trained study assistants will visit the participating practices regularly to collect data and to verify data quality by comparing antibiotic prescriptions and number of patient visits with software entries. After data collection, a second study assistant will check the data file for completeness and correctness.

### Statistical methods

A ‘full analysis set’ (FAS) following the principle of intent-to-treat (ITT) will include every patient as randomised. First, confirmatory analyses on efficacy variables will be performed on the FAS patients. Because imbalances are more likely among cluster-randomised trials than among trials randomised at the patient level, variables related to dentists’ characteristics will already be included in the primary data analysis. Initially, baseline characteristics will be compared between groups. If significant differences are found for variables that could potentially bias the results, data analysis will be based on a comparison of the baseline-adjusted rates of antibiotic prescribing between the intervention and the control group at T1 (primary outcome) and T2. The direct maximum likelihood approach is used as estimation procedure and will provide unbiased estimated values. Analyses for secondary endpoints will be performed in a strictly exploratory way using analogue models.

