## Methods

### Trial design

A cluster-randomised controlled trial (cRCT) will be performed. Clusters are employed to avoid contamination between the intervention and the control group. Each cluster will consist of one general dentist practice and all of its patients during a defined period. Prior to randomisation, baseline data will be collected over a period of six months (T0) to adjust for inter-cluster imbalances of antibiotic prescribing. After randomisation, the intervention takes place which is followed by two more six-month periods of collecting antibiotic prescribing data (T1 and T2).

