### Randomisation

Cluster-randomisation takes place after baseline data collection. Concealment of allocation is preserved. Randomisation will be stratified by the antibiotic prescribing rates of the participating dental practices and will be performed by a statistician; this will avoid imbalances between the intervention and the control group.

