### Outcomes

Primary outcome is the overall antibiotic prescribing rate of the intervention group and the control group measured at T1, thus measured in the interval between months one to six after intervention. A number of secondary outcomes will be analyzed for the subgroup of patients suffering from odontogenic infections (see below).

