### Sample size

Data from Northern Germany shows that about 6% of all patients cared for in general dentistry receive antibiotics [11]. A relative reduction of 20% is perceived as both clinically relevant and attainable. For comparison, the previous CHANGE cRCT on antibiotic prescribing in German primary care reached a relative reduction of 40% [14]. The estimated intra-class correlation coefficient (ICC) of the prior CHANGE trial was employed for sample size calculation in this trial. In a RCT randomising at patient level and aiming at a reduction of antibiotic prescribing from 6% to 4.8% (a relative reduction of 20%) about 5,750 patients per group are necessary (power = 80%, level of significance (two-sided) α = 5%). Using an ICC of 0.2 and a cluster size of 1,000 patients the sample size needs to be adjusted with an average design factor of 4. Thus a total sample size of 46,000 patients in 46 dental practices is necessary for the trial. Assuming a dropout rate of 20% initially, 58 practices need to be recruited for baseline (see Figure 1).

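### Baseline adjustment of the primary T1 comparison should be fixed in advance, not switched on by a significance test of baseline characteristics

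*Protocol article*

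**What the plan says.** Four statements in the protocol article bear on this.

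- Trial design gives the purpose of the pre-randomisation period: "baseline data will be collected over a period of six months (T0) to adjust for inter-cluster imbalances of antibiotic prescribing". No condition is attached.
- Randomisation: "Cluster-randomisation takes place after baseline data collection", and "Randomisation will be stratified by the antibiotic prescribing rates of the participating dental practices". The stated aim is to prevent imbalance between the arms. The number of strata is not given.
- Statistical methods includes some covariates unconditionally: "variables related to dentists’ characteristics will already be included in the primary data analysis". It does not say whether the practice's own T0 prescribing rate is one of them.
- Statistical methods then sets a sequence: "Initially, baseline characteristics will be compared between groups", followed by "If significant differences are found for variables that could potentially bias the results, data analysis will be based on a comparison of the baseline-adjusted rates" at T1 and T2. The test, its level (practice or patient), the significance threshold and the list of variables are not named.

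The primary outcome is fixed elsewhere: "Primary outcome is the overall antibiotic prescribing rate of the intervention group and the control group measured at T1".

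**The concern.** This is a stated decision rule, so a fuller analysis plan that followed it would inherit the problem.

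First, the criterion is wrong. After randomisation, any baseline difference between arms is due to chance, and a p-value for it says nothing about whether the variable predicts the outcome. Prediction of the outcome is what makes adjustment worthwhile.

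Second, the confirmatory model becomes data-dependent. It is not known until baseline p-values have been seen, the set of potentially biasing variables is open, and the Blinding section says that statisticians are not blinded.

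Third, the sections do not fit together. Trial design collects T0 in order to adjust. Randomisation balances the prescribing rate. Statistical methods then makes adjustment wait for an imbalance that the stratification is meant to prevent.

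At stake is mainly precision. If neither T0 nor the strata are in the model, the standard error, test and interval give no credit for what T0 explains.

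**Working it through.** **The plan's own figures.** Inputs from Sample size: 6% against 4.8%, 80% power, two-sided 5%.

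- n = [1.960·√(2·0.054·0.946) + 0.842·√(0.06·0.94 + 0.048·0.952)]² / 0.012² = 5,568 per group, or 5,734 with continuity correction. The plan says about 5,750.
- 5,750 × 2 × 4 = 46,000 patients, or 46 practices of 1,000. 46 / 0.8 = 57.5, so 58 recruited.
- A design factor of 4 at 1,000 patients per practice implies ICC = (4 − 1)/999 ≈ 0.003. The stated ICC of 0.2 would give 1 + 999 × 0.2 = 200.8. That mismatch is a separate matter. I use 0.003 because the planned 46 practices rest on the factor of 4.

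**Simulation.** 46 practices of 1,000 patients, beta-binomial practice rates, ICC 0.003, 4,000 runs per setting. Assumed, because the article does not give them: 2, 3 or 4 equal-sized T0 strata with balanced allocation; T0-T1 correlation of true practice rates of 0.6, 0.8 or 0.95; a practice-level t-test as the unadjusted analysis; ANCOVA on the T0 rate as the adjusted one. The rule simulated is ANCOVA only if the T0 t-test has p < 0.05. Without stratification or adjustment, power is 0.78-0.80, which matches the planned 80%.

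**How often a T0 test is significant (ICC 0.003).**

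| Strata | Practice-level test | Patient-level test ignoring clustering |
|---|---|---|
| none | about 5% | about 32% |
| 2 | about 0.1-0.3% | 11-12% |
| 3 | 0 of 4,000 | about 5% |
| 4 | 0 of 4,000 | 2-3% |

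**Other variables.** With j independent tests at 5%, P(at least one significant) = 1 − 0.95^j: 23% for j = 5, 40% for j = 10.

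**Consequence (ICC 0.003, range over 2-4 strata).**

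| True-rate correlation | Power, rule | Power, strata in model | Power, T0 always in model | Type I error, rule | Type I error, T0 always in model |
|---|---|---|---|---|---|
| 0.6 | 0.81-0.82 | 0.85-0.87 | 0.88 | 0.032-0.037 | 0.047-0.051 |
| 0.8 | 0.82-0.83 | 0.89-0.91 | 0.93-0.94 | 0.024-0.027 | 0.051-0.057 |
| 0.95 | 0.84 | 0.92-0.96 | 0.98 | 0.011-0.022 | 0.048-0.049 |

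The Monte Carlo standard error at 5% is √(0.05 × 0.95/4,000) ≈ 0.003.

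**Where the precision goes (correlation 0.8, 3 strata, 20% effect).** The SD of the estimate is 0.00425 unstratified and unadjusted, 0.00355 stratified and unadjusted, and 0.00333 with ANCOVA. Share of the attainable variance reduction achieved by stratification alone: (0.00425² − 0.00355²)/(0.00425² − 0.00333²) ≈ 0.78. The stratified but unadjusted analysis still reports a mean SE of 0.00420. Since 0.00420/0.00355 ≈ 1.18, its intervals are about 18% too wide.

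**At the stated ICC of 0.2** (correlation 0.8), power is below 0.10 either way: 0.02-0.03 under the rule, 0.08-0.09 with T0 in the model.

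**The case against.** The strongest reply is that the default branch is not the bare t-test simulated here. Dentist characteristics are in the primary analysis regardless, the T0 rate might be counted among them, and the strata might enter a model that a condensed article does not show. This stands in part. No passage says that the strata are left out, so the losses above are conditional on neither T0 nor strata being modelled. But if the T0 rate were already included, the conditional sentence would have little purpose.

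The simulated trigger is also narrower than the stated one, which covers any potentially biasing variable. That stands: adjustment would be switched on more often than simulated, so the figures overstate the average loss. It does not rescue the rule, because switching by chance is itself the defect.

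A reader might infer that stratification practically guarantees adjustment never happens. The article does not support that. It names no test level, and a patient-level test is significant in 2-12% of stratified trials at ICC 0.003 and 83-88% at ICC 0.2.

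A reader might also infer that the trial throws away most of its baseline information. It does not. In the setting shown, stratification alone secures about three quarters of the attainable variance reduction. What may be lost is credit for it in the inference.

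Finally, power under the rule (0.81-0.84) is still at the planned 80%, and the simulated test is conservative, so no excess of false positives is shown.

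**Conclusion.** The concern holds in this form: the primary analysis is made to depend on a baseline significance test, which is the wrong criterion, makes the confirmatory model data-dependent and is at odds with the unconditional purpose given for T0. The contradiction and the data-dependence follow from the text alone.

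The size rests on assumptions. With ICC about 0.003, 2-4 strata, true-rate correlations of 0.6-0.95, a T0-only trigger and no covariates in the default model, the rule costs roughly 6 to 14 points of power and gives a test below its nominal level. Fixed adjustment gave higher power in every setting tried. Larger ICCs change the absolute power, but the article offers no firm basis for choosing one. Should-fix: the harm shown is lost efficiency and avoidable analytic discretion, not a biased or anti-conservative primary test.

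**What to change.** Delete the significance-test condition. State that the primary T1 model always includes the practice's T0 prescribing rate as a fixed covariate (and the strata, if wanted), alongside the dentist characteristics already planned, and list those characteristics. Report the T0-unadjusted comparison as a sensitivity analysis, and present baseline characteristics descriptively without tests.

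The cost is about one sentence. By the Trial status section, T0 data were already collected and T1 collection was still running, so no new data are needed. The change should be dated before T1 outcomes are examined by arm.

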### Process evaluation

After T1 a short standardised questionnaire and some qualitative in-depth interviews with dentists of the intervention group will be performed. The interviews will focus on the usefulness and usability of the material offered during the intervention seminar (*e.g.*, standard fax form for dentist-physician communication or patient information material) and the way dentists made use of it. Recommendations for improvement will also be collected. The interviews will be recorded, transcribed, and analysed.

### Ethical approval

The study was approved by the Ethics Committee of the Rostock University Medical Center in December 2012 (Approval-No. A 2012-0147).

### Study registration

The study has been registered with Current Controlled Trials Ltd. with the reference ISRCTN09576376.

### Trial status

Currently (the end of 2013), the baseline data have been collected, the participating dentists have been randomised, and the dentists of the intervention group have been trained. The T1 data collection period has started. The data on T1 will be collected by the end of the T1 six-month period in spring 2014.

## Discussion

In light of rising levels of antibiotic resistance worldwide, reducing the number of non-indicated prescriptions of antibiotics is highly relevant. A substantial part of antibiotic resistance is caused in primary care [17,18]. This has an impact on secondary healthcare as well: the increasing antibiotic resistances in ambulatory care cause a growing use of broad-spectrum antibiotics in hospitals, a process that fosters further resistance development. Although several previous studies have aimed at reducing antibiotic prescribing in general practice and/or pediatrics [1,12-14], so far hardly any initiative has focused on dentistry. This is rather surprising, because dentistry accounts for a comparatively high amount of antibiotics and witnesses increasing resistance levels among dental pathogens. By means of a complex educational intervention, the DREAM trial takes up this fact and aims at optimising antibiotic prescribing behaviour of general dentists in Germany.

The modeling of the intervention is based on concepts, such as communication training or prescribing feedback, that have already proven their efficiency in reducing non-indicated antibiotic prescribing in general practice [13,14]. By performing narrative in-depth interviews and focus group discussions with dentists, these concepts have been adapted to the specific setting of dentistry. Dentist-patient communication, for example, is subject to specific constraints: During treatment, patients usually have few possibilities to talk to their dentist. As a consequence, gestures and facial expressions as well as communication at the beginning and at the end of the consultation are especially important. The intervention seminar takes these specific conditions into account.

As to bacterial resistance development of oral streptococci, very little research exists. A study by Chardin *et al.* found that, in a healthy population, treatment with amoxicillin—which is commonly used in dentistry—increases antibiotic resistance [19]. The study on antibiotic resistance of oral streptococci performed in this trial will enhance evidence in this field. Results of these analyses will be communicated to dentists and—by means of a positive competition—are assumed to have a positive impact.

## Conclusion

In case of positive evaluation, the intervention seminar developed for the DREAM trial might serve as a theoretically grounded and efficient concept tested for feasibility and acceptability. Consequently, it might be integrated into graduate and post-graduate education. Because the intervention seminar is easy to implement and demands relatively little time from the dentists, it might be transferred to other healthcare systems. This way, the approach might contribute to a sustainable reduction of antibiotic prescribing in general dentistry.

## Abbreviations

DID: Daily defined doses per 1000 inhabitants per day; FAS: Full analysis set; ICC: Intra-class correlation coefficient; ITT: Intention-to-treat (analysis); RCT: Randomised controlled trials.
